## Abstract

**Background:**

Improved colorectal cancer (CRC) survival rates have been reported over the last years, with more than half of these patients surviving more than 5 years after the initial diagnosis. Better understanding these so-called long-term survivors could be very useful to further improve their prognosis as well as to detect other problems that may cause a significant deterioration in their health-related quality of life (HRQoL). Cure models provide novel statistical tools to better estimate the long-term survival rate for cancer and to identify characteristics that are differentially associated with a short or long-term prognosis. The aim of this study will be to investigate the long-term prognosis of CRC patients, characterise long-term CRC survivors and their HRQoL, and demonstrate the utility of statistical cure models to analyse survival and other associated factors in these patients.

**Methods:**

This is a single-centre, ambispective, observational follow-up study in a cohort of *n* = 1945 patients with CRC diagnosed between 2006 and 2013. A HRQoL sub-study will be performed in the survivors of a subset of *n* = 485 CRC patients for which baseline HRQoL data from the time of their diagnosis is already available. Information obtained from interviews and the clinical records for each patient in the cohort is already available in a computerised database from previous studies. This data includes sociodemographic characteristics, family history of cancer, comorbidities, perceived symptoms, tumour characteristics at diagnosis, type of treatment, and diagnosis and treatment delay intervals. For the follow-up, information regarding local recurrences, development of metastases, new tumours, and mortality will be updated using hospital records. The HRQoL for long-term survivors will be assessed with the EORTC QLQ-C30 and QLQ-CR29 questionnaires.

An analysis of global and specific survival (competitive risk models) will be performed. Relative survival will be estimated and mixture cure models will be applied. Finally, HRQoL will be analysed through multivariate regression models.

**Discussion:**

We expect the results from this study to help us to more accurately determine the long-term survival of CRC, identify the needs and clinical situation of long-term CRC survivors, and could be used to propose new models of care for the follow-up of CRC patients.

## Background

Cancer is one of the most frequent diseases worldwide and is one of the main causes of hospital admissions. According to GLOBOCAN data, there were a total of 18.1 million new cancer cases and 9.6 million cancer deaths in 2018 [1]. In both sexes combined, colorectal cancer (CRC) is the fourth most commonly diagnosed cancer and the fifth leading cause of cancer-related death [1]. Advances in the diagnosis and treatment of cancer patients have generally increased patient survival rates. Indeed, according to the American Cancer Society (ACS), the 5-year survival rate after a cancer diagnosis is around 65% for all tumours, as well as for CRC in particular [2]. EUROCARE-5 data indicates that in Europe, the survival rate 5 years after diagnosis exceeds 50% for most tumour sites [3]. According to this report, the age-standardised 5-year survival rate for colon cancer was 57 and 55.8% for rectal tumours [3].

Despite these figures, very few prospective studies have evaluated the recurrence or mortality rates in survivors of CRC [4]. Although controversial, a patient with an oncological process diagnosis is currently considered ‘cured’ when they survive 5 years after diagnosis [5], with these patients often being referred to as ‘long-term survivors’. Thus, in CRC, standard follow-up strategies are usually performed periodically during this period [6]. However, other authors suggest that this ‘cure’ is not guaranteed for patients who survive the first 5 years after diagnosis and that follow-up strategies should be modified according to the risk factors presented by each patient [4]. Thus, it would be useful to use a rigorous methodology to determine, in greater detail, the probability (or percentage) of cured patients, i.e. long-term CRC survivors, as well as the variables associated with the prognosis of both these and ‘non-cured’ patients in order to establish more appropriate follow-up strategies.

Kaplan–Meier curves and the Cox proportional hazard models are the statistical methods most commonly used to analyse all-cause mortality in cancer studies, while a competing-risk analysis is preferred to determine cause-specific mortality and its associated factors [7]. However, cure models, which are still not often used, provide an alternative statistical tool to estimate the cure rates of cancer patients and analyse the differences between those individuals who are long and short-term survivors, as well as to identify covariates associated differently with short or long-term progosis [8]. Although some authors have highlighted the usefulness of cure models as an analysis strategy which could provide especially useful information for quantifying the improvement in survival figures in CRC [9], very few publications are available in this regard. These studies show cure rates of around 50% and a median survival rate for uncured patients of about 1 year after diagnosis [9–13]. No such studies have been undertaken in Spain, and furthermore, most of this work has been carried out using population registries and/or do not include clinical information other than the age at diagnosis, sex, and disease stage, and therefore, have not used these models to explore the impact of other covariates on cure rates or survival time.

Data evaluating the long-term health-related quality of life (HRQoL) of CRC survivors are also scarce, although work studying the first 5 years after their diagnosis is more common [14]. Recent work suggests that these patients present a HRQoL similar to that of the general population, although some factors such as intestinal dysfunction can contribute to their deterioration, even 15 years after their initial diagnosis [14]. Furthermore, these results should be contrasted with those obtained in other cohorts and in different locations. Therefore, this study was planned with the aim of determining the long-term prognosis in CRC patients, to characterise long-term survivors and their HRQoL, and demonstrate the utility of statistical cure models in the study of CRC survival. Results from this study may be useful to determine the cure rate (proportion of long-term survivors) in CRC, the survival rates of ‘uncured’ patients and associated factors, and to develop a predictive model to identify long-term survivors from among CRC patients. In addition, it will also allow us to describe HRQoL and the prevalence of symptoms in these patients.

## Methods/design

### Objectives

The goals of this project are
i.To determine the long-term survival rates of CRC patients and the variables associated with the prognosis.ii.To ascertain the cure rate (proportion of long-term survivors) for CRC and the survival rate for uncured patients as well as the factors associated with these by using mixture cure models.iii.To develop a predictive model to identify long-term survivors from among patients diagnosed with CRC.iv.To determine the HRQoL and prevalence of symptoms in long-term survivors of CRC.

### Design

This is a single-centre follow-up observational study of cases of CRC diagnosed in the Complexo Hospitalario Univesitario A Coruña (A Coruña, northwest Spain) from 2006 to 2013 (*n* = 1945), previously included in some of our other research projects [15–17]. A quality of life sub-study will be carried out in the patients included in the framework of one of these other projects [17] who have not died at the time of this present study (*n* = 485), in order to assess their current HRQoL and compare it with their baseline HRQoL scores when the CRC was initially diagnosed.

### Inclusion and exclusion criteria

Every case of CRC diagnosed during the 2006–2013 period was included. We excluded prevalent or recurrent cases, multiple cancer cases, cases detected by CRC screening, and cases diagnosed in another hospital but referred to our centre for treatment.

### Sample size

A cohort of *n* = 1945 incident CRC cases is available from previous research projects. Assuming exposure of 50% and a censored data percentage of 58% [3, 18], this sample size will make it possible to use a Cox regression model to detect significant changes with a hazard ratio (HR) of 1.22 or more (security = 95%; statistical power = 80%). Based on the available survival figures of the *n* = 485 patients included in a previous project for whom baseline HRQoL data are available [17], we estimate that around *n* = 281 patients will still be alive at the time of this proposed study. Assuming loses of around 30%, to estimate HRQoL with 95% confidence and at ±7% precision, we estimate that some *n* = 200 patients will need to be included in this HRQoL sub-project.

### Data collection

Cases were identified via the Pathological Anatomy Service at our hospital and the specialists who followed-up the patients were also responsible for their recruitment. After signing their informed consent to participation, we interviewed the patients and reviewed their primary and specialised care clinical history. We already have a computerised database in which we have collected the information from the framework of our other research projects [15–17]. In the case of the HRQoL sub-study, non-deceased patients will be informed of the objectives of this present study during one of their follow-up visits to the hospital. The HRQoL questionnaires will be completed after they grant their informed consent to participation in this new study.

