### Measurements

Information about each patient was obtained in our previous studies and is detailed in our other publications [15–17]. This data includes
Sociodemographic data: age at the time of the CRC diagnosis, sex, civil status, and education level.Patient interview data: perceptions and attitudes to the first symptoms of CRC.Personal or family history of cancer or other neoplasms.Comorbidities (Charlson comorbidity index).Disease presentation variables: first symptoms/signs, access to primary and specialised care, first consultation service, examinations and complementary tests prior to the diagnosis, laboratory tests at the time of the diagnosis.Diagnosis and treatment delay.Tumour characteristics at the time of diagnosis: tumour size, site, histological grade, macroscopic appearance, permeation, stage (TNM and Dukes), location of metastases, and infiltration of adjacent organs.Surgical treatment: curative or palliative surgery, type of surgery, access route (laparoscopic vs. open CRC surgery), type of anastomosis, resection of other viscera, resectability, surgical border infiltration, surgical morbidity, and reinterventions and their causes.Chemotherapy or radiation treatments.Complementary tests during follow-up: hospital consultations and physical examinations, laboratory tests, chest X-rays, abdominal ultrasound, colonoscopies, computed tomography, barium enema, and positron emission tomography.

The follow-up data that will be updated in this project include mortality (global and specific), local recurrences, distant metastases, and new-onset neoplasms, together with the date of each of these events. Non-deceased patients will be censored at the end of follow-up or on the latest date for which evidence is available for that patient.

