In addition to the data described above, we will also record information about the HRQoL for the patients in the quality of life sub-study (*n* = 485 CRC patients diagnosed from 2010 to 2013) 3 to 6 months from the time of the CRC diagnosis. HRQoL measurements are also available 1 year after diagnosis for *n* = 214 of these patients, and 2 years after the diagnosis in *n* = 195 patients. For the patients in this sub-cohort who are still alive when this project is carried out, information will be collected about their current HRQoL using the general module of version 3.0 of the *European Organization for Research and Treatment of Cancer* (EORTC) *QLQ-C30* questionnaire [19] which is applicable to all cancer patients. We will also apply the EORTC QLQ-CR29 module which is specific to colon and rectal cancer patients [20].

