### Statistical analysis

#### Overall and cancer-specific survival analysis

Overall survival will be analysed using Kaplan–Meier curves, bivariate log-rank tests, and multivariate Cox proportional-hazards models. For cancer-specific and disease-free survival, a competing risk analysis will be performed. The cumulative incidence of CRC-related death in the follow-up will be estimated considering death from other causes as a competing risk, using the method proposed by Kalbfleisch and Prentice [21]. Disease-specific mortality will be compared according to different characteristics, using Gray’s test [22]. Finally, a multivariate analysis will be performed using the model proposed by Fine and Gray [23].

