#### Cure models

The cure rate and ‘latency’ (time to death or recurrence) will be estimated using parametric and semi-parametric mixture cure models [8]. For parametric models, logistic regression will be used to analyse the cure fraction and the Weibull distribution will be used to model the survival probability of uncured patients. For semi-parametric analysis, long-term survival will be modelled using a Cox proportional-hazards model. The following results will be obtained from the estimates of the models, (a) the cure rate; (b) relative survival curves for all the patients and for uncured patients; (c) median survival rates in uncured patients; and (d) the timepoint at which 90% of the uncured patients have died. Estimates will be obtained for each sex and CRC location (colon vs. rectum), according to age (15–49, 50–59, 60–69, 70–79, and 80–99), and year of diagnosis. Using these models, the effect of different covariates on the cure rate and survival of the uncured patients will be determined independently. The parameters of the model will be estimated using the maximum likelihood method.

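### The article says all CRC cases were included but describes entry by consent and interview; if entry required surviving to consent, survival and cure counted from diagnosis would be biased upwards.

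*Protocol article*

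**What the plan says.** Three places in the protocol article describe who is in the cohort.

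- Inclusion and exclusion criteria: "Every case of CRC diagnosed during the 2006–2013 period was included", subject to listed exclusions.
- Data collection: cases were found through the pathology service, "the specialists who followed-up the patients were also responsible for their recruitment", and then "After signing their informed consent to participation, we interviewed the patients and reviewed their primary and specialised care clinical history".
- Abstract, Methods: "Information obtained from interviews and the clinical records for each patient in the cohort is already available in a computerised database from previous studies".

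On timing, Measurements places the HRQoL questionnaire of the 485-patient subset at "3 to 6 months from the time of the CRC diagnosis". No interval between diagnosis and entry is given for the other patients. The same section fixes the end of observation: "Non-deceased patients will be censored at the end of follow-up or on the latest date for which evidence is available for that patient". It gives neither a time origin nor an entry time.

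On analysis, "Overall survival will be analysed using Kaplan–Meier curves, bivariate log-rank tests, and multivariate Cox proportional-hazards models". Cancer-specific mortality is analysed with Gray's test and the Fine and Gray model, and relative survival with Ederer II. The cure rate and latency "will be estimated using parametric and semi-parametric mixture cure models". None of these sections mentions delayed entry. The limitations in the Discussion are the single centre and information bias; selection by consent or survival is not among them.

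**The concern.** The descriptions do not fit together. A patient who died, or was too ill, before the specialist could obtain consent belongs to a cohort of all cases, but cannot have been interviewed. As Data collection is written, consent also comes before the record review.

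If the consent and interview description is the accurate one, every cohort member was alive at some point after diagnosis. Any time between diagnosis and that point is then free of deaths by selection. Standard estimators that start the clock at diagnosis would count it as time at risk. The missing deaths are early ones, which in a mixture cure model come from the uncured, so the error has one direction: survival and the cured share come out too high. A larger sample does not reduce it.

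The main result is at stake. The Discussion names accurate estimation of long-term survival as the primary endpoint, and the Objectives add the cure rate.

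**Working it through.** **1. The plan's own figure.** Sample size states a detectable HR of 1.22 with n = 1945, 58% censored, 50% exposed and 80% power.
- Events = 1945 × 0.42 = 817.
- Schoenfeld, two-sided 5%: detectable HR = exp[(1.960 + 0.842) × 2 / √817] = 1.217.

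The figure reproduces. It does not depend on the entry rule, so it says nothing for or against the point. The plan gives no figure for the effect of entry itself.

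**2. Inputs for the illustration.**
- Cured fraction c = 0.50 and uncured median 1 year: the Background's summary of other published studies.
- Exponential survival of the uncured: an assumption. The plan names the Weibull, so shape is varied in step 4.
- Entry lag L: an assumption of 1, 3 or 6 months. Only the 3 to 6 months of the HRQoL subset is in the article.

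**3. Same lag for everyone.** Survival from diagnosis is S(t) = 0.5 + 0.5 × 2^(−t), t in years. Among patients alive at L, the apparent cure rate is 0.5 / S(L), and apparent 5-year survival is S(5) / S(L), with S(5) = 0.5 + 0.5/32 = 0.516.

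| Lag | S(L) | Lost before entry | Apparent cure (true 50%) | Apparent 5-year survival (true 51.6%) |
|---|---|---|---|---|
| 1 month | 0.972 | 2.8% | 51.4% | 53.1% |
| 3 months | 0.920 | 8.0% | 54.3% | 56.0% |
| 6 months | 0.854 | 14.6% | 58.6% | 60.4% |

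**4. Shape of the uncured curve.** With Weibull shapes from 0.7 to 1.2 and the same median, apparent cure runs from 50.9% (shape 1.2, 1 month) to 60.5% (shape 0.7, 6 months).

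**5. Lag only in the HRQoL subset.** The subset is 485/1945 = 24.9% of the cohort; the other 1460 are given no lag.
- 3 months: 0.249 × 54.3% + 0.751 × 50% = 51.1%.
- 6 months: 0.249 × 58.6% + 0.751 × 50% = 52.1%.

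**6. Does delayed entry repair it?** Four million patients were simulated from the exponential model, for which true 5-year survival is 51.6%.

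| Entry lag | Naive 5-year survival | Delayed-entry Kaplan–Meier |
|---|---|---|
| Uniform, 0 to 3 months | 53.8% | 51.6% |
| Uniform, 3 to 6 months | 58.2% | 56.1% |

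When some patients enter soon after diagnosis, delayed entry recovers the true value. When nobody is observed before 3 months it cannot: the result is in effect survival conditional on reaching 3 months, S(5)/S(0.25) = 56.0%.

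**The case against.** The strongest reply is that the bias is not shown to exist. Cases were identified through pathology, which can capture early deaths, and the data combine interviews with clinical records. The cohort comes from several previous projects whose publications carry the detail. If patients who died before consent were kept from records, the inclusion statement is true and nothing is truncated. The time origin is not stated, so the absence of delayed entry is inferred from silence, and a condensed article may leave that to the full protocol or SAP. All of this stands, and it is why the point is conditional. It does not remove the conflict between the inclusion statement and the description of consent and interview data for each patient, which is in the text itself.

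A reader might infer that the whole cohort entered at 3 to 6 months, so that the cure rate is overstated by 4 to 9 points. The article does not support this: that interval is given only for the 485. They were diagnosed over four years, about 121 a year, against about 243 a year for the whole cohort (1945 over eight years), which suggests that the questionnaire condition did not apply to everyone.

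A reader might also count the exclusion of screen-detected and multiple-cancer cases, or the timing of the HRQoL questionnaire, as further survivor bias. The exclusions are declared scope choices. The HRQoL sub-study aims at current quality of life in people alive years later, all of whom necessarily passed the 3 to 6 month point.

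Finally, delayed entry does not correct for refusal of consent and may not recover survival from diagnosis (step 6). That stands, and it shapes the fix.

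**Conclusion.** The point holds in conditional form. The article describes its cohort in two ways that cannot both be literally true, and which one is right decides whether the planned analyses are biased. If entry required survival to consent and time runs from diagnosis without delayed entry, overall, relative and cancer-specific survival and the cure fraction are biased upwards for any positive lag in which deaths occur.

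The size is illustrative. Under the exponential assumption it is about 1 to 9 points on the cure rate for lags of 1 to 6 months in everyone, and about 1 to 2 points if only the HRQoL subset was affected. It rests on the Background's 50% and 1 year, on the assumed shape, and on lags that are not stated for three quarters of the cohort. That the published estimates will be inflated is a further step which the document does not establish.

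**What to change.** 1. Reconcile the Abstract, the Inclusion and exclusion criteria and Data collection. State whether eligible cases who died, were too ill or refused before consent are among the 1945, and how many there were. State the time origin and the entry date.
2. If such cases are not included, enter each patient in the risk set at the consent or interview date in the Kaplan–Meier, Cox, competing-risk and relative-survival analyses. Condition the cure likelihood on survival to that date.
3. Where entry dates are missing, or nobody enters early, choose a landmark and report survival and cure conditional on reaching it.
4. Where records permit, add a sensitivity analysis on all pathology-identified cases. This is also the only step here that bears on refusal.
5. List consent and survivor selection as a limitation.

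The cost is one date variable and standard software options, provided that the dates can be retrieved from projects covering diagnoses back to 2006, which the article does not show. The statistical price is wider intervals in the first months and, where early entry is absent, a conditional estimand in place of survival from diagnosis.

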### Measurements

Information about each patient was obtained in our previous studies and is detailed in our other publications [15–17]. This data includes
Sociodemographic data: age at the time of the CRC diagnosis, sex, civil status, and education level.Patient interview data: perceptions and attitudes to the first symptoms of CRC.Personal or family history of cancer or other neoplasms.Comorbidities (Charlson comorbidity index).Disease presentation variables: first symptoms/signs, access to primary and specialised care, first consultation service, examinations and complementary tests prior to the diagnosis, laboratory tests at the time of the diagnosis.Diagnosis and treatment delay.Tumour characteristics at the time of diagnosis: tumour size, site, histological grade, macroscopic appearance, permeation, stage (TNM and Dukes), location of metastases, and infiltration of adjacent organs.Surgical treatment: curative or palliative surgery, type of surgery, access route (laparoscopic vs. open CRC surgery), type of anastomosis, resection of other viscera, resectability, surgical border infiltration, surgical morbidity, and reinterventions and their causes.Chemotherapy or radiation treatments.Complementary tests during follow-up: hospital consultations and physical examinations, laboratory tests, chest X-rays, abdominal ultrasound, colonoscopies, computed tomography, barium enema, and positron emission tomography.

The follow-up data that will be updated in this project include mortality (global and specific), local recurrences, distant metastases, and new-onset neoplasms, together with the date of each of these events. Non-deceased patients will be censored at the end of follow-up or on the latest date for which evidence is available for that patient.

In addition to the data described above, we will also record information about the HRQoL for the patients in the quality of life sub-study (*n* = 485 CRC patients diagnosed from 2010 to 2013) 3 to 6 months from the time of the CRC diagnosis. HRQoL measurements are also available 1 year after diagnosis for *n* = 214 of these patients, and 2 years after the diagnosis in *n* = 195 patients. For the patients in this sub-cohort who are still alive when this project is carried out, information will be collected about their current HRQoL using the general module of version 3.0 of the *European Organization for Research and Treatment of Cancer* (EORTC) *QLQ-C30* questionnaire [19] which is applicable to all cancer patients. We will also apply the EORTC QLQ-CR29 module which is specific to colon and rectal cancer patients [20].

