#### Relative survival

Relative survival will be estimated as the ratio of observed survival of CRC patients and the survival that would have been expected if the patients had had the same mortality rate as the general population. The expected survival will be estimated from the population mortality rates estimated for the health area by age group, sex, and study year, using the Ederer II method [24]. Following other publications, the ‘statistical cure’ point will be defined as the point at which the relative survival curve plateaus, e.g., when the patients remaining alive experience the same mortality rate as the age and sex-matched population without cancer [9–13]. Thus, the value at which the plateau is achieved will provide an estimation of the curation rate.

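### Living patients are censored at their last evidence date, deaths are not, and hospital records are the only mortality source named: this can bias long-term relative survival and the cure fraction in either direction

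*Protocol article*

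**What the plan says.** On the source of follow-up data, the abstract's Methods paragraph says that "information regarding local recurrences, development of metastases, new tumours, and mortality will be updated using hospital records". No section names a death register, a population register or active tracing. The Data collection section describes the earlier projects in the past tense: "we interviewed the patients and reviewed their primary and specialised care clinical history".

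On censoring, the Measurements section says: "Non-deceased patients will be censored at the end of follow-up or on the latest date for which evidence is available for that patient". It sets no corresponding date after which a death would no longer count.

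On the length of routine contact, the Background, speaking of the first 5 years after diagnosis, says that "in CRC, standard follow-up strategies are usually performed periodically during this period".

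On use of the tail, the Relative survival section says: "The expected survival will be estimated from the population mortality rates estimated for the health area by age group, sex, and study year". It adds that "the value at which the plateau is achieved will provide an estimation of the curation rate". The Cure models section also asks for the time by which 90% of uncured patients have died. The Discussion makes an accurate estimate of long-term survival, with the factors related to cure, the primary endpoint.

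**The concern.** The main results are read from the years in which routine hospital contact usually thins out. Two mechanisms can distort that period.

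- **Unequal limits for living and dead.** Suppose a well patient's records stop at year 5 or 6. If the patient is alive, follow-up ends there. If the patient dies at year 9 and the death reaches the records, follow-up runs to year 9 and the death counts. Among patients who have left, those who will die stay in the risk set and those who live are removed, so late mortality is overstated and the plateau is pulled down.
- **Unequal ascertainment of observed and expected deaths.** Expected survival comes from population mortality, which is not limited to deaths known to a hospital. If some of the cohort's deaths outside the hospital never reach the records, observed mortality is too low against its comparator and relative survival is pushed up.

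At stake are the cure fraction, the level and existence of the plateau, and the survival of uncured patients.

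**Working it through.** The plan gives no figure for the share of patients lost or of deaths found, so there is none to reproduce. Its sample-size figures do not depend on this point. What can be checked is whether the rule as written can move the result, and which way.

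**Inputs.** From the Background, which reports published cure-model studies: cure about 50%, median survival of uncured patients about 1 year. Assumed: Weibull shape 0.8 for uncured patients, constant other-cause hazard of 0.03 per year, potential follow-up spread evenly over 6 to 14 years. All shares of loss and of missed deaths below are also assumed. Relative survival is the Kaplan–Meier estimate in 200,000 simulated patients divided by expected survival. The cure fraction is fitted with a Weibull mixture cure model for relative survival in 40,000 of them.

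**True values.** The Weibull scale is 1/(ln 2)^(1/0.8) = 1.58 years. Uncured survival at 10 years is exp(−(10/1.58)^0.8) = 0.0126. Relative survival at 10 years (RS10) is 0.5 + 0.5 × 0.0126 = 0.506. Expected survival is exp(−0.3) = 0.741, so overall survival is 0.506 × 0.741 = 0.375. Complete vital status to one closing date returns RS10 0.505 and cure 0.499.

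**Living patients cut at last contact.** A share of patients leaves hospital follow-up at year 5 to 6, and later deaths are captured fully, half the time or never:

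| Share leaving | RS10, all late deaths captured | RS10, half captured | RS10, none captured | Cure, all captured | Cure, none captured |
|---|---|---|---|---|---|
| 25% | 0.479 | 0.491 | 0.504 | 0.474 | 0.499 |
| 50% | 0.435 | 0.467 | 0.506 | 0.418 | 0.502 |
| 75% | 0.351 | 0.411 | 0.503 | 0.241 | 0.501 |

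The columns with none captured are the symmetric case: neither late deaths nor late survival count, leaving is unrelated to prognosis, and there is no bias. With 50% leaving and all late deaths captured, the time by which 90% of uncured patients have died reads 7.9 years instead of 4.5.

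**Deaths missed.** A share m of all deaths goes unrecorded, and the patient is either censored at a last visit up to half a year earlier or carried alive to the closing date:

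| m | RS10, last visit | Cure, last visit | RS10, carried alive | Cure, carried alive |
|---|---|---|---|---|
| 5% | 0.530 | 0.524 | 0.547 | 0.543 |
| 10% | 0.556 | 0.549 | 0.589 | 0.581 |
| 20% | 0.611 | 0.604 | 0.675 | 0.660 |

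A closed form checks the last-visit column. If missed deaths are censored at the moment of death, the observed hazard is (1 − m) times the true one, so observed survival is 0.375^(1 − m). Dividing by 0.741 gives 0.532, 0.558 and 0.616, close to the simulated values.

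If only other-cause deaths are missed, at 20%, the observed background hazard is 0.024 against an expected 0.030. RS10 is then 0.506 × exp(0.006 × 10) = 0.538, and relative survival drifts upward instead of levelling.

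**Both together.** With 10% of deaths before last contact missed and 50% of patients leaving, fitted cure is 0.464 if all late deaths are captured and 0.550 if none are.

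**The case against.** Four arguments stand against the point.

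- **The article does not say that hospital records are the sole source.** This is right. A reader might infer that deaths are traced only there, but the text excludes nothing. Primary care histories were used in the earlier projects, and the evidence in the censoring rule is not limited to hospital evidence. What stands is narrower: the sentence on the new mortality update names hospital records and no other source.
- **Censoring at last contact is conventional and need not bias anything.** This is also right, and the symmetric columns show it. But that result needs the same limit for living and dead, and the stated rule does not secure it.
- **The 5-year limit describes usual practice, not this hospital's records.** This is fair. The Data collection section expects to meet sub-study survivors at hospital follow-up visits, so contact may continue for some. That lowers the share affected without removing the asymmetry. The 30% losses assumed for the sub-study may include refusals and cannot be read as loss to mortality follow-up.
- **The Discussion concedes possible information bias from clinical records.** It does so in general terms and mentions neither missed deaths nor informative censoring.

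A reader might also infer that the cure rate will be uninterpretable. The documents do not support that: the two mechanisms oppose each other, and no share of loss is given.

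**Conclusion.** The point holds as a weakness in a stated rule, not as a demonstrated bias. The censoring date is limited for living patients and not for deaths, and the comparator is population mortality. The estimands lie largely beyond the usual period of routine contact.

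Under the assumed shares, a true cure fraction of 0.50 can read anywhere from 0.24 (75% leaving, all late deaths captured) to 0.66 (20% of deaths missed and carried alive). It stays at 0.50 if loss is non-informative and symmetric. Those ends come from deliberately wide assumptions; the shares, Weibull shape, constant background hazard and follow-up span are not in the documents. Neither size nor sign can be settled from the text. No figure in the plan is wrong on this account. Severity: should be fixed, before the mortality update is closed.

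**What to change.** - Ascertain vital status for all 1945 patients from a source that does not depend on hospital attendance, preferably death-register linkage, up to one common closing date.
- Where that check is complete, censor patients confirmed not dead at the closing date in the overall, relative and cure analyses of death. Keep the last clinical evaluation as the censoring date only for recurrence and metastasis.
- If linkage is unavailable or incomplete, do not carry unverified patients alive to the closing date: the working shows that this inflates cure more than censoring at the last visit does (0.660 against 0.604 at 20% missed). Instead, end follow-up for living and dead alike at the last systematic vital-status check, and do not count deaths found after it.
- Report completeness of follow-up.

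The cost is one linkage request with its approval and some delay. No new patients or procedures are needed.
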